## **9 LAIV-induced immune responses**

Although the exact correlates of protection from influenza illness following intranasal LAIV are not clear, existing data suggest that mucosal immune responses play a key role [7, 32-34]. Lower serum antibody titres are generated following LAIV when compared with inactivated influenza vaccination, despite the greater efficacy seen following LAIV in children [35, 36]. Several studies demonstrate the efficacy of LAIV in the absence of a robust serological response [32, 37, 38] and LAIV-induced nasal IgA responses were shown to protect from culture-confirmed influenza [7, 32]. The heterogeneity of sample collection techniques and IgA assay methodology make interpretation of many studies difficult. Robust and well-validated methods are therefore required for future exploration of LAIV-induced mucosal immunity. Potent cell mediated immunity is also elicited by LAIV but not inactivated influenza vaccines [35, 39, 40] and may also mediate protection from subsequent influenza [35].

## **10 Potential effects of the nasopharyngeal microbiome on LAIV immunogenicity**

The reasons for geographical variation in vaccine responses are not fully understood and might have implications not only for influenza, but also for other mucosally delivered live vaccines. Emerging data from studies of the oral rotavirus vaccine, which show similar variation in protective efficacy, indicate that gut microbiome variability may explain the suboptimal responses observed in resource-limited countries [41, 42]. Interactions between gut microbiota, innate and adaptive immunity are recognized [43-46], but little is known about how changes in human nasopharyngeal microbiota might influence responses to vaccines delivered to the URT.

Murine data suggest that URT commensal bacteria can impact innate and adaptive immunity following intranasal wild-type influenza challenge in several ways [47-49]. Firstly, by providing

priming signals via Toll-like Receptors, often required for transcriptional activation of genes in the NLRP3-inflammasome-caspase-1 pathway [49]. Commensal bacteria also calibrate the activation thresholds of innate antiviral responses in macrophage interferon-signaling pathways [47]. These can impact on downstream virus-specific T-cell [47, 49] and nasal IgA responses [47], although the mechanisms for the latter are not clear. Possibilities include altered T-follicular helper cell help to germinal centre B-cells producing IgA or altered signaling from nasal epithelial cells leading to T-cell independent class-switch recombination.

Establishing whether similar relationships exist between nasopharyngeal microbiota and post-LAIV immunity in humans has the potential to explain both inter-individual response variability and why live mucosal vaccines perform poorly in resource-limited settings. It can also provide avenues to develop strategies for improving mucosal vaccine responses in the future via modulation of nasopharyngeal microbiota and/or circumventing these immunological defects via adjuvantation.

## **11 Potential effects of LAIV on nasopharyngeal microbiota**

The human URT is a dynamic and complex environment, where communities of commensal and potentially pathogenic organisms co-exist. Bacterial and viruses are able to colonise this niche, dependent on interactions with other microbes and host factors. In a steady state, this dynamic process has no adverse consequences for the host and can provide beneficial effects influencing immune function [50], but imbalances can result in pathogenic species outgrowth and subsequent respiratory and invasive disease [51, 52]. Interactions between influenza and bacteria (E.g. *S. pneumoniae* and *S. aureus*) are well documented, resulting in secondary bacterial pneumonia [53, 54]. This is partly explained by an increase in nasopharyngeal bacterial carriage [55] due to epithelial barrier disruption [56, 57], increase in conditions favouring bacterial adhesion [58] and modulation of host innate immunity resulting in increased bacterial load [59-61].

The immediate effects of LAIV on the nasopharyngeal microbiome, however, are less clear. Although an attenuated virus, LAIV infects nasal epithelial cells and parallels some aspects of wild-type influenza host-pathogen interactions. Mouse models show that LAIV induces changes in nasopharyngeal microbiota, temporarily changing pneumococcal and staphylococcal bacterial burden in a similar way to wild-type influenza [62], possibly due to increased type I interferon, known to play a key role in enhanced bacterial colonization [55]. Whereas there are no safety concerns regarding LAIV leading to bacterial pneumonia given the hundreds of thousands of children who have received this vaccine, a temporary increase in bacterial burden could have implications on onward transmission in areas of high pneumococcal colonization, resulting in greater rates of pneumococcal colonization at a population level. Although underpowered, a recent study from a cohort of UK children given LAIV suggested similar observations may be seen in human studies [63]. In a setting like The Gambia where pneumococcal colonisation in children is extremely high [64], this interaction needs to be explored and results used to form the basis for more complex pneumococcal transmission studies if widespread LAIV use is considered.

## **12 Rationale**

The WHO considers young children as a priority for influenza vaccination in developing countries [2]. In this context, data from high-income countries show that intranasal LAIV is more effective in children at preventing influenza than IIV [21, 65]. No robust data exist on the immunogenicity of LAIV in children from sub-Saharan Africa, where influenza infection in young children is common but no vaccine is currently in routine use. Limited data suggest that

the efficacy of intranasal LAIV may not be as robust in this setting as in higher resource settings where the majority of studies have been conducted.

Cutting edge bioinformatic methods used in systems biology now allow in depth exploration of the relationship between early innate gene expression and later adaptive responses to vaccines, highlighting previously unrecognised links between these two aspects of immunity. [name], a collaborator on this study, has used such techniques to identify novel associations between early expression of the kinase CaMKIV post-TIV and systemic anti-influenza antibody responses, as well as the B-cell growth factor *TNFRS17* and neutralizing antibody responses following Yellow Fever vaccination [66, 67]. To optimize responses in future generations of influenza vaccines, more detailed insights into the mechanisms associated with mucosal protection are required. Applying systems vaccinology methods to clinical studies of LAIV in African children would provide a means of dissecting the mechanisms by which better mucosal immunity may be elicited by intranasal vaccines in this setting.

## 13 Aims and Objectives

### 14 Study objectives

#### 15 Primary

- (i) To identify novel early systemic and mucosal molecular signatures following LAIV that are associated with subsequent robust nasal and oral influenza-specific immunoglobulin A (IgA) responses, in order to provide insight into the mechanisms of successful mucosal immunization.
- (ii) To identify associations between nasopharyngeal microbiota and nasal and oral influenza-specific IgA responses post-LAIV in Gambian children, to explore whether microbiome variability can explain suboptimal immune responses in some individuals to live intranasal mucosal vaccines in Sub-Saharan Africa.
- (iii) To establish whether LAIV impacts the nasopharyngeal microbiome, with a specific focus on the burden of *S. pneumoniae*.

#### 16 Exploratory

- (i) To identify novel early systemic and mucosal molecular signatures following LAIV that are associated with subsequent robust serum haemagglutination inhibition (HI) responses.
- (ii) To identify novel early systemic and mucosal molecular signatures following LAIV that are associated with subsequent robust influenza-specific T-cell responses.
- (iii) To describe the association between LAIV virus shedding at day 2 and/or 7 following immunization (as a measure of vaccine ‘take’) and influenza-specific mucosal IgA, serum HI and systemic influenza-specific T-cell responses to LAIV.

- (iv) To explore the impact of antibiotic modulation of microbiota on LAIV-induced nasal gene expression and downstream effects on the mucosal immunogenicity of LAIV.
- (v) To establish whether LAIV increases the burden of *S. aureus* in the nasopharynx.
- (vi) To explore associations between nasopharyngeal microbiome profiles and post-LAIV nasal and systemic gene expression profile changes.
- (vii) To explore whether the presence of respiratory viruses in the nasopharynx at the time of LAIV administration impacts on influenza-specific mucosal IgA, serum HI and systemic influenza-specific T-cell responses to LAIV
- (viii) To establish whether an expansion in peripheral T-follicular helper (pTfh) cells occurs following LAIV.
- (ix) To explore whether early systemic monocyte expansion following LAIV is associated with subsequent robust mucosal IgA responses.
- (x) To explore whether an expansion of IgA-expressing B-cells with a mucosal-homing phenotype is detectable in blood following LAIV and whether this expansion correlates with the subsequent nasal and oral influenza-specific IgA response.
- (xi) To explore how interferon-induced transmembrane protein-3 (IFITM3) host gene polymorphisms may impact on early innate and later influenza-specific immune responses induced by LAIV.
- (xii) To explore the correlation between systemic HI and oral fluid immunoglobulin G (IgG) responses, to assess the suitability of the latter as a proxy measure of LAIV-mediated seroconversion obtained via non-invasive means.
- (xiii) To explore any differences in early post-LAIV gene expression signatures and influenza-specific adaptive responses post-LAIV (nasal and oral IgA, serum HI or influenza-specific T-cell) in children who acquire laboratory-confirmed influenza following immunization and those who do not. Data will be obtained by passive surveillance and laboratory testing of nasopharyngeal swabs of children who go on to develop ILI as defined by:
  - Sudden onset of fever of  $\geq 38^{\circ}\text{C}$  (axillary) AND
  - either a cough or sore throat

## 17 Study endpoints

### 18 Primary endpoints

- Influenza-specific nasal IgA responses at day 21 post-LAIV
- Oral fluid IgA and IgG responses at day 21 post-LAIV
- Gene expression changes in nasal and systemic samples at day 2 following LAIV
- Nasopharyngeal microbiome profiles at baseline, day 7 and day 21 following LAIV
- Density of *S. pneumoniae* before and after LAIV as established by quantitative polymerase chain reaction (PCR)

## 19 Exploratory endpoints

- Influenza-specific serum HI responses at day 21 post-LAIV
- Influenza-specific peripheral T-cell responses at day 7 and 21 post-LAIV
- Detectable vaccine virus (A/H3N2, A/pH1N1 and B) in nasopharyngeal samples obtained at day 2 and 7 post-LAIV, as determined by real-time reverse transcriptase polymerase chain reaction (rRT-PCR)
- Respiratory viruses present in the nasopharynx at vaccination as determined by multiplex rRT-PCR (e.g. parainfluenza, adenovirus, coronavirus, rhinovirus)
- Nasopharyngeal microbiome profiles at baseline and at day 28 following a single dose of oral azithromycin in n = 30 individuals
- Frequency of pTfh cells at day 7 and 21 following LAIV
- Frequency of peripheral monocyte subsets at day 2 following LAIV
- Frequency of B-cell subsets, IgA and mucosal homing marker expression at day 7 and 21 following LAIV
- IFITM3-rs12252 genotyping (CC, CT and TT polymorphisms) by amplification and sequencing of genomic DNA
- Detectable influenza (A/H3N2, A/pH1N1 and B) in nasopharyngeal samples obtained from children presenting with ILI during follow up period
- Density of *S. aureus* before and after LAIV as established by quantitative polymerase chain reaction (PCR)

## 20 Study design

### 21 Type of study and design

All primary objectives and most exploratory objectives will be addressed through the conduct of a phase 4, randomized, controlled clinical vaccine trial. A total of 330 healthy children aged 24 – 59 months will be enrolled into one of three groups of equal size (3 x 110 children):

- (i) LAIV-vaccinated (Group A - blood sample at day 0, 2, 21)
- (ii) LAIV-vaccinated (Group B - blood sample at day 0, 7, 21)
- (iii) Control group (Group C)

Allocation concealment will be maintained from the start through the use of sealed envelopes. Block randomization stratified by sex will be used and a randomization sequence will be generated by an MRC Statistician not involved in the study. Investigators will not be blinded to group allocation from this point onwards as the sampling schedule differs between groups. Local laboratory staff will therefore not be blinded for this reason, but samples sent to external laboratories will be blinded (see section 3.2.3).

Two LAIV-vaccinated groups are included in order to achieve several exploratory objectives, which require blood sampling at different time points following vaccination, whilst minimizing the number of times children are bled times (i.e. 2nd blood sample at either day 3 or day 7 post-LAIV, but not both). The unvaccinated subjects will serve as a control group for the primary objective of assessing the impact of LAIV on the nasopharyngeal microbiome. Section 8 details the statistical considerations made to decide on the sample sizes to be recruited. The vaccination and sampling schedules for groups A, B and C are detailed in Tables 1.

Group C subjects will be administered LAIV after the NPS is taken on their day 21 visit, to offer them the same level of protection against influenza illness by participating in the study as those in groups A, B and D.

An additional 35 healthy children aged 24 – 59 months will be recruited in the 2nd phase of recruitment (Jan – June 2018) to assess the objective of how modulation of the nasopharyngeal microbiome with antibiotics impacts the mucosal immunogenicity to LAIV

(Group D – vaccination and sampling schedule in Table 2), by administration of a single dose of oral azithromycin 28 days prior to receiving LAIV. This timeframe has been chosen based on pilot data from the the Gambia showing significant alternation in the nasopharyngeal microbiome approximately 1 month after single dose oral azithromycin in Gambian children aged 1 – 7 years in mass trachoma treatment campaigns ([name], unpublished, personal communication). These subjects will be matched as closely as possible by pre-antibiotic nasopharyngeal microbiome profile [1], age (24 – 35, 36 – 47, 48 – 59 months) and sex (in that hierarchical preference), in a nested case-control study, to n = 35 children recruited in the main clinical trial. This will be done after all children have been recruited and microbiome sequencing and analysis has been completed. To avoid allocation bias of these controls, an individual in the [name] laboratory blinded to the immunogenicity data will undertake this matching process. In brief, the microbiome profile matching will be performed by first categorizing which of eight described profiles each child's microbiome clusters with depending on the dominant taxa (e.g. *Staphylococcus*, *Streptococcus*, *Moraxella* etc.) as described previously by the [name] group [1].

The day 2 visit window for groups A, B and D is deliberately restrictive to allow both blood and NPS to be taken at a time when peak gene expression changes post-LAIV can be captured. The other visit windows are intentionally liberal to maximize the opportunity to obtain a full set of blood and NPS samples for the purpose of the analysis, whilst in each case, not compromising the scientific objectives they are designed to deliver. However, in each case, the intention will be to obtain the sample on or as close to the day specified as possible. The sampling schedule and associated laboratory assays to be performed on each clinical sample is detailed in Table 3. The procedure to deal with participants who default visit windows is discussed in section 5.4.

Participants in groups A and B (n = 110 each) will be enrolled for approximately 4 –10 months: 21 days of active participation during recruitment months January – June 2017 or January – June 2018, followed by attendance at the Sukuta Health Centre for assessment of any ILI that occurs up to the 31st of October in the year of recruitment into the study. This design has been chosen as data from Senegal show that peak influenza transmission occurs between July and October each year ([name], XVII International Symposium on Respiratory Viral Infections, Vancouver, CA, 2015).

Group C will be enrolled for 21 days, with participation finishing following the day 21 visit and receipt of LAIV (Table 1). Group D (n = 35) will be enrolled for approximately 4 – 10 months: 49 days of active participation during recruitment months January – June 2018, followed by attendance at the Sukuta Health Centre for assessment of any ILI that occurs up to 31.10.18. Those individuals presenting with possible ILI will have a limited history taken and if a sudden onset of a fever of  $\geq 38^{\circ}\text{C}$  (axillary) *and* either a cough or sore throat is present, a nasopharyngeal swab will be taken and diagnostic viral rRT-PCR performed.

The vaccine to be studied (Nasovac-S) has a WHO pre-qualification certificate and marketing authorization for the study population. However, the trial will provide detailed information on the determinants of immunogenicity and therefore inform the design of future generations of similar live intranasal influenza vaccines.

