**Table 3. Sampling schedule and use of clinical samples in laboratory assays**

| Visit timing from LAIV
(window) | Clinical Sample | Laboratory assays                                                                                                                                                                                              |
|--------------------------------------------|------------------------|-----------------------------------------------------------------------------------------------------------------------------------------------------------------------------------------------------------------------|
| Day 0 visit                                | Oral swab              | Influenza-specific IgA and IgG                                                                                                                                                                                        |
|                                            | NPS^                   | Nasopharyngeal microbiome
Influenza-specific IgA
Host transcriptomic profiling
Viral multiplex RT-PCR                                                                                                        |
|                                            | Blood sample (5ml)     | Innate cell profiling (FC)
Influenza-specific T-cell responses (FC)
B-cell phenotyping (FC)
Peripheral T-follicular helper cells (FC)
Host transcriptomic profiling
Serum haemagglutination inhibition |
| Day 2 visit
(+ 1 day)                   | NPS                    | Host transcriptomic profiling
LAIV virus shedding (RT-PCR)                                                                                                                                                         |
|                                            | Blood sample (5ml)     | Innate cell profiling (FC)
Host transcriptomic profiling                                                                                                                                                           |

|                            |                    |                                                                                                                                                        |

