### **50 Selection and withdrawal of participants**

#### **51 Selection of participants**

The study will randomize 330 children between 24 and 59 months, followed by sequential recruitment of a further 35 children within the same age range (see section 3.1), which allows for approximately 10% participant attrition during the study and required sample sizes to achieve primary objectives (Section 8). Screening of potentially eligible children will continue until this number or the recruitment end date (30.06.2018) is reached. Recruitment will take place over two six month periods, January – June 2017 and January – June 2018 (first subject first visit, FSFV to last subject first visit, LSFV of each season). These months have been chosen to coincide with periods when wild-type influenza infections are likely to be at their lowest, therefore least likelihood of interference with study endpoints. The recruitment target for season 1 (January – June 2017) will be 195 children (65:65:65 into groups A, B and C) and season 2 (January – June 2018) 170 children (45:45:45 into groups A, B and C, followed by 35 into group D – see section 3.1). This represents 29 – 33 children per month or approximately 7 - 8 children per week. Any shortfall in numbers caused by lack of recruitment or withdrawal in season 1 will be made up in season 2 by increasing target numbers.

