#### **121**    Identifying novel early systemic and mucosal signatures following LAIV that are associated with robust nasal and oral influenza-specific IgA responses

A precise power calculation is difficult to perform as a number of markers will be studied in an unbiased analysis, rather than testing whether a single defined marker is associated with vaccine endpoints. Microarrays will be performed (peripheral blood and NPS-derived RNA) on a subset of children at the opposite ends of the IgA response spectrum following LAIV (n = 30 in each group), thus identifying those at the extremes of response. A further 30 children, given azithromycin, will also have microarrays performed at baseline and day 2 following LAIV and results compared to n = 30 age, sex and baseline microbiome profile-matched children.

[name] has successfully identified markers of vaccine immunogenicity in cohorts of

similar or smaller sizes than those proposed following several vaccines including LAIV, IIV, yellow fever and polysaccharide-based meningococcal vaccines [66, 67, 71]. Over 2000 genes were differentially expressed at day 3 post-LAIV when compared to baseline [66].

Although there are no data in Gambian children given LAIV to use in sample size calculations, estimates can be provided based on microarray data from healthy Gambian children (2 – 59 months) recruited as controls in a pneumonia study ([name], unpublished data), which is the best available data to use. The *ssize* package [72] in R was used to estimate the number of children required to identify differentially expressed genes between two groups. Using the strict Bonferroni correction to adjust for multiple testing, 30 subjects in each group is required to ensure that at least 90% of genes (of 49,386) have a power of  $\geq 90\%$  at  $\alpha 0.01$  to detect a 2-fold change (see Figure 1 below). Using the more relaxed false discovery rate to control for multiple testing, 10 subjects in each group would be sufficient.

[figure not shown]

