**Figure 1. Sample size estimates to detect 2-fold gene expression changes**

## 122 Identifying associations between nasopharyngeal microbiota and nasal and oral influenza-specific IgA responses post-LAIV in Gambian children, to explore whether microbiome variability can explain suboptimal immune responses in some individuals

Calculations were performed using the Shiny application for determining sample size calculations for case-control microbiome studies (<https://fedematt.shinyapps.io/shinyMB/>) [73]. Simulations were run using the anterior nares-derived microbiome data available on the application, estimating that analyses would consider the most abundant 150 operational taxonomic units (OTUs). IgA responders and non-responders were defined as cases and controls respectively and sample size/power calculations performed to detect a 1.5-fold

difference in abundance in the 10 most abundant OTUs and 2-fold difference in abundance in the next 10 most abundant OTUs, between the two groups (Figure 2).

Power calculations were performed using these parameters, for a range of sample sizes from 50 – 150 per group and using the Wilcoxon-Mann-Whitney (WMW) test applied to each OTU individually and the resulting *P*-values multiplicity adjusted with the Benjamini and Hochberg method to control the false discovery rate ('WMWavg' – Figure 3). Prior data suggest that approximately 50% of children receiving LAIV are IgA responders, using a definition of  $\geq 2$ -fold rise in IgA from baseline [7]. At an alpha of 0.05, 82 subjects per group would give a power of 80%. A sample size of  $n = 100$  per group was selected (i.e.  $n = 200$  children given LAIV, accounting for approximately 50% showing an IgA response), which even accounting for some drop outs would give a power of  $\geq 80\%$ .

If required, the complexity of data may be reduced by defining microbiota composition according to 8 distinct profiles described by the [name] group [1] rather than variability across 20 different OTUs/species, thus reducing the need for correction for multiple testing and increasing the power significantly.

[figure not shown]

**Figure 2. Simulations of anterior nares derived microbiome data showing differences between cases and controls of the 20 most abundant OTUs.**

[figure not shown]

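### The azithromycin comparison (exploratory objective (iv)) uses only 35 matched comparators and does not match on recruitment year, although about 198 LAIV children, about 81 of them from 2018, will have the same IgA data

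*Combined protocol and SAP*

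**What the plan says.** Section 21 (Type of study and design) adds 35 children in the second recruitment season, who receive azithromycin 28 days before LAIV. On their comparators it says: "These subjects will be matched as closely as possible by pre-antibiotic nasopharyngeal microbiome profile", then by age band and sex, "in a nested case-control study, to n = 35 children recruited in the main clinical trial". The matching is done after sequencing is complete, by someone who does not see the immunogenicity results. The Protocol Summary repeats the 35 matched comparators. Recruitment year is not a matching factor.

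Section 23 recruits Group D after Groups A, B and C are complete, within January to June 2018. Section 51 plans 65 children each in Groups A and B for 2017 and 45 each for 2018. Section 27 says that the vaccine strains may be updated between the seasons.

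Tables 1 to 3 give Groups A, B and D the same day 0 and day 21 nasal and oral swabs, with oral swabs assayed for "Influenza-specific IgA and IgG" and nasopharyngeal swabs for IgA. The day 2 and day 7 shedding swabs and the microbiome swabs are also common to the three groups. Section 122 plans microbiome and IgA response in 200 "children given LAIV, accounting for approximately 50% showing an IgA response".

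Only the arrays are limited to a subset. Section 121 says that 30 azithromycin children "will also have microarrays performed at baseline and day 2 following LAIV and results compared to" those of 30 matched children. No analysis method is stated for objective (iv).

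**The concern.** Objective (iv) (section 16) covers nasal gene expression and, downstream of it, mucosal immunogenicity. For gene expression, array numbers limit the comparators. For IgA they do not: the assays are already planned in every LAIV child, and profile, age and sex will be known for all of them by the time the match is made. Stopping at 35 leaves about 160 measured children out of the comparison, and the plan gives no reason.

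The second weakness is season. Group D is all 2018, and its comparators may come from either year. Any difference in IgA response between years, whether from vaccine strains, circulating viruses or laboratory batches, would then be read in part as an effect of azithromycin.

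This is the trial's only azithromycin contrast, in healthy children who, as section 157 acknowledges, do not need the antibiotic themselves.

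**Working it through.** The plan gives no power or precision for this contrast, so there is no figure to reproduce. As a check on the counts, 110 + 110 + 35 = 255 vaccinated, which agrees with section 101.

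**Inputs**
- Groups A and B: 2 × 110 = 220 children. Section 51 sets the recruitment totals, "which allows for approximately 10% participant attrition during the study", so 220 × 0.9 = 198.
- 2018 children in A and B: 45 + 45 = 90, and 90 × 0.9 = 81. The other 198 − 81 = 117 are from 2017. Share planned for 2017: 130/220 = 59%.
- Group D: 35 × 0.9 = 31.5, taken as 31.
- Assumed, because the documents give none: one continuous outcome in SD units, equal SDs, two-sided α 0.05.

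**Precision before adjustment.** SE = √(1/n₁ + 1/n₂); detectable difference at 80% power ≈ (1.96 + 0.84) × SE.

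| Comparison | SE (SD units) | Change in SE | Detectable difference |
|---|---|---|---|
| 31 v 31 | 0.254 | – | 0.71 SD |
| 31 v 81 (2018 only) | 0.211 | −17% | 0.59 SD |
| 31 v 198 (both years) | 0.193 | −24% | 0.54 SD |

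**Precision after adjustment.** No Group D child is from 2017. Once year is in the model, the 2017 children therefore help only to estimate the effects of profile, age and sex, and the contrast rests on the 2018 children. Simulation with 31 Group D children, 117 comparators from 2017 and 81 from 2018, eight unequal profiles, three age bands and sex (profile frequencies assumed) gave:
- all children, year in the model: SE 0.216, which is 1 − 0.216/0.254 = 15% below 1:1;
- 2018 children only: SE 0.221, or 13% below;
- all children, year left out: SE 0.198, or 22% below.

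Other simulated settings put the first two at 11 to 13%. Together with the unadjusted 17%, the defensible range is 11 to 17%. The SE is then 0.211 to 0.226 and the detectable difference 0.59 to 0.63 SD, against 0.71 SD.

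**Season.** If year plays no part in choosing comparators, about 59% come from 2017. For an assumed shift of 0.4 SD between years and no azithromycin effect, the bias is 0.4 × 0.59 = 0.24 SD.
- 1:1 match: 0.24/0.254 = 0.93 standard errors, which gives a false-positive rate of about 15%. Simulation gave 14 to 18%.
- All 198 children, year left out: the same bias with a smaller SE, 0.24/0.193 = 1.22, which gives about 23%. Simulation gave 21%.
- Year in the model, or 2018 children only: 5 to 6% in simulation, with the bias removed.

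**The case against.** **Matching is the confounding control.** Group D is not randomized, and the match on profile, age and sex is the only stated protection. A reader might infer that the plan throws away a quarter of its precision for nothing. That does not follow. The match buys balance, and adding the other children unadjusted would trade bias for precision. What stands is narrower: the same factors can be controlled by regression in a larger set.

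**Thin cells.** Eight profiles, three age bands and two sexes make 48 cells. That is on average 198/48 = 4.1 comparators per cell, or 81/48 = 1.7 from 2018. In rare profiles, balance would rest partly on the model. This stands as a real cost.

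**Pairing can itself gain precision.** With within-pair correlation ρ, the matched SE is √(2(1 − ρ)/35). An unadjusted pool of 198 breaks even at ρ = 0.41, and one of 81 at ρ = 0.28. This counts against an unadjusted comparison. Regression on the matching factors removes the same variation.

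**Season weakens the larger pool.** Most of the extra children are from 2017. Table S2 shows a group-by-year interaction (p = 0.016) for pneumococcal density, a different endpoint, which suggests only that season can matter. This limits the gain, but the present match has the same exposure.

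**Nothing forbids a wider analysis.** Section 127 plans multivariable models of IgA response, and section 129 promises relevant covariates. Neither names Group D. The plan therefore does not exclude the other children, but it does not provide for them either.

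**One matched set keeps expression and IgA on the same children.** That suits the wording of the objective, and is a reason to retain the matched comparison as a sensitivity analysis.

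**Conclusion.** The point holds for nasal and oral IgA, with shedding as supportive. The plan names 35 comparators where about 198 measured children exist, about 81 of them from the same season, and its match leaves out year. A year-adjusted or 2018-only regression would reduce the SE by about 11 to 17%, given equal SDs and 10% attrition, and would remove the bias from a difference between years. It would not remove any drift within the 2018 season, because Group D is recruited last.

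Three stronger readings are not supported:
- A gain of about 24% requires no season effect and year left out of the model. The documents give no basis for assuming that.
- This is not the smallest comparison in the trial. The arrays at the extremes of IgA response are planned at 30 per group (section 121).
- Serum HI and T-cell responses are not part of objective (iv), and its gene-expression half gains nothing without more arrays.

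The objective is exploratory and has no stated effect size, so the consequence is moderate. The change is still worth making, because it needs no new data.

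**What to change.** In section 21, the Protocol Summary and the planned analyses:

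1. Keep the matched comparators for the 30 v 30 microarrays.
2. For nasal and oral IgA, and shedding as supportive, compare Group D with all eligible Group A and B children by regression adjusted for microbiome profile, age, sex and recruitment year; or restrict the comparators to 2018 children and adjust for the first three. Choose one as the main analysis before the IgA results are seen.
3. For Group D, use the day −28 profile as the baseline covariate, as the match does. The day 0 profile is measured after azithromycin.
4. Report the 1:1 matched comparison as a sensitivity analysis, with the number of comparators in each profile and from each year.

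The cost is analysis-plan wording, with no extra child, sample or assay. The downside is that balance in rare profiles depends partly on the model, which the counts in item 4 would make visible.
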